The study represents a confirmatory analysis, but due to the in-depth biomechanical and neurophysiological experimental measurements, the sample size calculation also includes a calculation of an additional sub-sample for the experimental protocol. In addition to the assessments listed in Table 7, they subsequently completed the balance tasks on the force plate and oscillating sensorimotor therapy device at each of the three measurement timepoints (see Table 6). In order to protect the patient collective of the study and avoid increased drop-out due to complex biomechanical and neurophysiological measurement technology, a reduced sample size was calculated on the basis of the effect strength of the preliminary study [11,14]. According to the effect size calculations of the Institute for Medical Statistics and Bioinformatics at the University of Cologne, the mean difference in BBS of 3.07 points (standard deviation (SD) = 1.04) of the IG and CG for a type 1 error rate of α = 1 % and a power of 1-β = 95 %, a required minimum sample size of N = 44 was calculated for the statistical F-test ANCOVA (fixed effects, main effects and interactions, two groups and five covariates) (95 % CI: 1.00–5.14, p = .004) assuming an effect size of f = 1.47 (df = 36, actual power = .95) [11,35]. Based on the ≈40 % drop-out rate of the preliminary study (N = 70) PP analysis (N = 41), a total of 70 patients (2x35) shall be randomized for in depth-biomechanical and neurophysiological measurements (during balance task and balance perturbation task) with a drop-out rate of around 40 %, to ensure a sufficient number of cases for this more extensive analysis [11]. Statistical evaluations will be carried out using the programs IBM SPSS 29 (IBM, Ehningen, Germany), R-Statistics (R Foundation, Vienna, Austria), JASP (JASP Team (2024), JASP (Version 0.19.3) [Computer software]) and Python [37]. Statistical methods for analyzing the primary outcome of change in balance performance after 12 units of therapy (change from baseline) will be covariance analyses (ANCOVA) (95 % confidence interval). The data will be analyzed with regard to an anchor-based approach of the minimal clinically important difference (MCID) of the BBS in individuals with MS (3 points according to Gervasoni et al., [38]. These analyses shall be verified by sensitivity analyses using linear mixed models (LMMs). Via this approach, incorporate fixed and random effects are being calculated to accurately represent non-independent data structures, to capture the change over the duration of therapy and follow-up. Therapeutic facility, gender, age, baseline BBS and EDSS score are included in the calculations as co-variables. This approach accommodates missing data under the missing at random (MAR) assumption, ensuring that all available measurements are included and therefore provide less biased and more robust estimates.

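### The sub-sample calculation treats a standard error of 1.04 as a standard deviation, so f = 1.47 is overstated 3.2 to 4.2 times and the stated 95% power at alpha 1% is unsupported

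*Protocol article*

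**What the plan says.** Section 2.8 gives two calculations. The main one assumes f = .40 and leads to N = 140. The second sizes a sub-sample for the force-plate, Posturomed and EEG measurements from a BBS result of the preliminary trial.

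- Effect: "the mean difference in BBS of 3.07 points (standard deviation (SD) = 1.04) of the IG and CG", with "95 % CI: 1.00–5.14, p = .004".
- Error rates: "type 1 error rate of α = 1 % and a power of 1-β = 95" per cent.
- Model: ANCOVA, "fixed effects, main effects and interactions, two groups and five covariates".
- Output: "a required minimum sample size of N = 44 was calculated", "assuming an effect size of f = 1.47 (df = 36, actual power = .95").
- Allowance for loss: about "40 % drop-out rate of the preliminary study (N = 70) PP analysis (N = 41"), from which "a total of 70 patients (2x35) shall be randomized for in depth-biomechanical and neurophysiological measurements".

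The number of patients behind the 3.07-point estimate is not given. The preceding paragraph of the section reports a different figure, 4.61 points, for the 41 per-protocol patients.

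**The concern.** An f of 1.47 for two groups means that the means differ by almost three standard deviations. The same section assumes f = .40 for the same scale and cites the same trial, where the larger difference of 4.61 points is called a large effect. A smaller difference should not carry an f more than three times as big. The likely explanation is that the precision of the estimated difference was entered in place of the spread between patients.

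This calculation is the only numerical basis for the sub-sample. The sub-sample carries the EEG hypothesis (secondary hypothesis 2) and the force-plate part of hypothesis 1. If the power statement stays, a null result there could be read as a negative finding from a comparison with 95% power at a 1% level, which the figures do not support.

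**Working it through.** **Inputs** (all from section 2.8): difference 3.07; stated SD 1.04; 95% CI 1.00 to 5.14; p = .004; alpha .01; power .95; two groups; five covariates; f = 1.47; N = 44; df = 36; 70 patients in 1:1 allocation; 40% loss.

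**1. Reproduce f.** For two equal groups f = difference / (2 × SD) = 3.07 / (2 × 1.04) = 1.476, which is the printed 1.47. So 1.04 was used as the between-patient SD.

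**2. Test whether 1.04 can be an SD.**
- CI half-width = (5.14 − 1.00) / 2 = 2.07. Divided by the t quantile: 2.07 / 1.995 = 1.037 (n = 70) or 2.07 / 2.023 = 1.023 (n = 41). That is the standard error.
- 3.07 / 1.04 = 2.95. The two-sided p is .0043 for n = 70, .0044 for n = 65 and .0053 for n = 41. The printed .004 fits 65 to 70 patients better than 41.
- If 1.04 were an SD, the standard error would be 1.04 × √(4/70) = 0.249, the CI about 2.57 to 3.57, and p far below .001. With n = 41 the CI would be about 2.41 to 3.73. Neither matches the printed interval.

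**3. Recover the SD and f.** With equal arms, SD = 1.04 / √(4/n). If the estimate was covariate-adjusted, this is the residual SD, which is the one that an ANCOVA calculation needs.

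| n behind 3.07 (assumed) | SD | f | 1.476 / f |
|---|---|---|---|
| 70 | 4.35 | 0.353 | 4.2 |
| 65 | 4.19 | 0.366 | 4.0 |
| 41 | 3.33 | 0.461 | 3.2 |

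**4. Power for the 3.07-point BBS effect.** Non-central F with λ = f² × N, numerator df 1 and error df N − 7 (two groups, five covariates).

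| n behind 3.07 | N for 95% at alpha .01 | Power at .01, N = 42 | Power at .01, N = 70 | Power at .05, N = 42 | Power at .05, N = 70 |
|---|---|---|---|---|---|
| 70 | 147 | 35% | 62% | 60% | 83% |
| 65 | 137 | 38% | 66% | 64% | 85% |
| 41 | 88 | 61% | 88% | 83% | 97% |

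**5. Try to reproduce N = 44.** With f = 1.47, alpha .01, power .95 and numerator df 1, the same formula returns N = 15; at N = 44 the power exceeds .999. Larger numerator df do not lead to 44 either: N = 17 for 2, 26 for 10 and 34 for 20. Two groups and five covariates at N = 44 leave error df 44 − 2 − 5 = 37, not 36.

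**6. Allowance for loss.** 70 × (1 − 0.40) = 42, below the stated minimum of 44. The inflation formula used for the main sample gives 44 / (1 − 0.40) = 73.3, so 74.

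**7. What 42 patients can detect.** For 80% power at two-sided alpha .05 with error df 35, f = 0.445, so d = 2 × 0.445 = 0.89.

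**The case against.** Several points on the other side stand.

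- A reader might infer that the inflated f produced N = 44. It did not: that f gives 15. One combination does return N = 44, df 36 and power .952, namely half of 1.47 (f = 0.735) with numerator df 2 and error df N − 8. The article does not state those settings. It shows a mislabelled standard error and an N that cannot be reproduced, not one slip that yields 44.
- A reader might state flatly that f is four times too large. That holds for about 65 to 70 analysed patients. The p-value and the separate per-protocol estimate of 4.61 favour this, but the number is not given, so the range is 3.2 to 4.2.
- A reader might conclude that the force-plate and EEG comparisons are badly underpowered. Every power figure here is for BBS. The article gives no effect size or SD for the instrumented measures, so their power is unknown rather than shown to be low.
- The 42-patient case takes the article's own 40% loss. The primary analysis set is the modified intention-to-treat population, and the main calculation anticipates 20% attrition. With 70 × 0.80 = 56 patients, BBS power on the 65-to-70 basis is 74 to 77% at alpha .05, and 83 to 85% with all 70. At alpha .01 it is 49 to 53% and 62 to 66%, so the stated claim still fails.
- Patient burden is given as a separate reason for a smaller sub-sample. That justifies limiting the number, but does not support the power figure.

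**Conclusion.** The point holds. The sentence's own interval and p-value identify 1.04 as a standard error, and f = 1.47 was built by treating it as an SD. The overstatement is 3.2 to 4.2 times, depending on an unstated n, with the upper end better supported. On every basis examined the 95% power at alpha 1% fails for the effect it was calculated for: 35 to 61% with 42 evaluable patients, 62 to 88% with all 70, and 88 to 147 patients needed. N = 44 and df = 36 do not follow from the stated inputs, and 42 retained patients would fall short of 44 anyway.

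The assumptions are equal arms, a single-df group comparison with five covariate df, and 41 to 70 patients behind the estimate. The error is confined to the sub-sample. The main N = 140 rests on f = .40 and is not touched by it, and nothing here establishes the power of the force-plate or EEG comparisons.

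**What to change.** Keep the 70 patients. In section 2.8:

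1. Relabel 1.04 as the standard error of the difference, and state the number of patients behind the 3.07-point estimate with the SD that follows.
2. Withdraw f = 1.47, N = 44, df = 36 and the claim of 95% power at alpha 1%.
3. State what the sub-sample can detect. With 42 evaluable patients, 80% power at two-sided 5% requires f of about 0.445 (d about 0.89). Say that no effect size was available for the instrumented measures.
4. Report force-plate and EEG group differences with 95% confidence intervals, so that a null result is not read as a negative from a 95%-power comparison.

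Calling these comparisons exploratory is optional. It would change the status of stated hypotheses, so it is a separate decision for the sponsor and not part of correcting the error.

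The cost is a change of wording with no added patients or procedures. The downside is that the stated power becomes less favourable.

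### Sub-sample calculation: N = 44, df = 36 and power .95 do not follow from the printed inputs of two groups, five covariates, f = 1.47, alpha 1 % and power 95 %

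*Protocol article*

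**What the plan says.** Section 2.8 of the protocol article (Statistical procedures) contains two sample size calculations. The main one, for the primary BBS analysis, uses an ANCOVA with two groups and five covariates, f = .40, alpha .05 and power .80. It reports N = 111 with df = 104.

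The second is for the sub-sample with force-plate, Posturomed and EEG measurements. Its inputs are "the mean difference in BBS of 3.07 points (standard deviation (SD) = 1.04) of the IG and CG", taken from the preliminary study with an interval and p-value of "95 % CI: 1.00–5.14, p = .004". The error rates are given as "for a type 1 error rate of α = 1 % and a power of 1-β = 95" %. The model is described as "fixed effects, main effects and interactions, two groups and five covariates". The result is "a required minimum sample size of N = 44 was calculated for the statistical F-test ANCOVA", "assuming an effect size of f = 1.47 (df = 36, actual power = .95"). The article then allows for a drop-out of about 40 % and sets the sub-sample at 70 randomized patients (2x35).

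**The concern.** The printed df can be checked by subtraction against the printed model, and it is off by one. The printed N and power can be checked against the printed f, and they are far off: an effect of f = 1.47 is so large that a handful of patients per arm would suffice.

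N = 44 is called the required minimum and is the base of the 2x35 target. The sub-sample carries the force-plate measure, which the primary hypothesis in section 2 (Methods) names alongside the BBS. As printed, a reader cannot tell which effect the sub-sample was sized for, and anyone who tries to verify the size will not reach 44.

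**Working it through.** **Inputs, all from section 2.8:** alpha .01; power .95; two groups; five covariates; f = 1.47; stated N = 44, df = 36, power .95. The numerator df is not printed. For a comparison of two arms it is 1, which is assumed first and then varied.

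**Method.** Fixed-effects ANCOVA by the non-central F distribution: non-centrality = f² × N, error df = N − groups − covariates, and the required N is the smallest with power of at least .95.

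**Step 1, error df.** Two groups and five covariates give N − 2 − 5 = N − 7. The main calculation follows this: 111 − 7 = 104. For the sub-sample, 44 − 7 = 37, not 36. A df of 36 at N = 44 means groups plus covariates = 44 − 36 = 8, not 7.

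**Step 2, trying to reproduce N = 44 from the printed inputs.** With f = 1.47, alpha .01, error df N − 7:

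| Numerator df | Required N | Power at that N |
|---|---|---|
| 1 | 15 (N = 14 gives .939) | .968 |
| 2 | 17 | .962 |
| 5 | 21 | .954 |
| 10 | 26 | .954 |

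None of these comes near 44.

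**Step 3, power at the printed N.** At N = 44, f = 1.47 and 1 numerator df, the non-centrality is 1.47² × 44 = 95.1 and power is above .9999, against .95 printed.

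**Step 4, settings that do give 44, 36 and .95.** With f = .735 (half of 1.47), 2 numerator df and error df N − 8, N = 43 gives .946 and N = 44 gives .952 with df = 36. This matches all three printed figures, but it is not the only match. Error df N − 8 arises from three groups with five covariates and equally from two groups with six covariate terms. Keeping N − 8, other numerator df also give a minimum of N = 44:

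| Numerator df | f giving N = 44, df = 36, power about .95 |
|---|---|
| 1 | about .67 |
| 2 | .732 to .742 |
| 3 | .778 to .789 |
| 5 | .850 to .863 |
| 10 | .984 to 1.000 |

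**Step 5, the effect size input.** 3.07 / 1.04 = 2.95, and half of that is 1.476, so the printed 1.47 comes from treating 1.04 as a between-patient SD. The half-width of the printed interval is (5.14 − 1.00) / 2 = 2.07, and 2.07 / 1.04 = 1.99. That is what one expects if 1.04 is the standard error of the difference. If it is, and if the preliminary result rested on 41 to 70 patients in equal arms (an assumption), then SD = 1.04 × √(N/4) = 3.33 to 4.35 and f = 3.07 / (2 × SD) = .46 to .35. The required N at alpha 1 %, 95 % power and 1 numerator df is then about 88 to 147.

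**Step 6, what the planned sub-sample can detect.** 70 × (1 − .40) = 42 evaluable. With two groups, five covariates, 1 numerator df, alpha .01 and power .95, N = 42 detects f = .68.

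**The case against.** The strongest objection is that N = 15 depends on a numerator df the article does not print, and that the authors may not have used 1. Their main calculation supports this: N = 111 at f = .40 is reproduced with 10 numerator df (power .802), whereas 1 numerator df gives 52. This stands, and 15 must be labelled an assumption. It does not close the gap, because 10 numerator df with f = 1.47 gives 26.

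It can also be said that 44 is conservative against f = 1.47, that only the experimental sub-sample is affected and not the N = 140 for the primary analysis, and that the effect size input matters more. All three are fair. But conservatism holds only if 1.47 is right, and Step 5 gives reason to doubt that. Correcting the effect size alone would still leave a df that contradicts the stated model.

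Three stronger readings are tempting and are not supported:

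- A reader might infer that the software was run for three groups at half the effect. The exact halving is suggestive, but other settings fit equally well and the actual entry is not in the article.
- A reader might infer that df = 36 is impossible in a two-arm trial. It is not: one more covariate or interaction term gives it, and therapeutic facility, with eight sites, could take more than one term depending on coding. What df = 36 contradicts is the stated two groups and five covariates.
- A reader might infer that, because 44 exceeds 15, recruitment is safe. That depends on f = 1.47, and the 88 to 147 in Step 5 lies above 70.

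**Conclusion.** The sub-sample calculation is wrong as printed. The df is 36 where the stated model gives 37. The required N is 15 with 1 numerator df, or 17 to 26 with 2 to 10, where 44 is printed. With 1 numerator df, power at N = 44 is above .9999 where .95 is printed. The df mismatch needs no assumption beyond the printed model. The N mismatch holds for every numerator df from 1 to 10. Which settings produced 44, 36 and .95 remains unknown.

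The direction of any correction to the required size is also open. It falls if f = 1.47 is kept, and rises if 1.04 proves to be a standard error; the 88 to 147 rests on that reading and on the assumed preliminary sample. The point should be corrected, but it does not touch the size calculated for the primary analysis.

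**What to change.** Check against the preliminary study whether 1.04 is an SD or a standard error, and derive f from the correct quantity. Rerun the sub-sample calculation with two groups, 1 numerator df and five covariates, or with the true number of covariate terms if facility is coded by site. Print the numerator df, f, error df, N and power from that single run.

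If 70 is kept for practical reasons, say so, and replace the N = 44, df = 36 and power .95 figures with the effect detectable at the expected evaluable number: about f = .68 at 42 evaluable, alpha 1 % and 95 % power.

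The work is one check of a source figure, one rerun and a rewritten sentence. The text should not state that the required size is unchanged until the rerun with a verified SD has been done.

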
The secondary study endpoints will be examined using descriptive statistical methods. Furthermore, to complement the primary analysis, an analogous ANCOVA will also be performed for secondary study endpoints. For the quality of life questionnaire (MSQoL-54), an MCID of 1.5 and 2.5 points will be applied [39]. Three procedures are applied to analyze the study results: (1) the *modified* intention-to-treat population (*m*ITT), which comprises all registered patients who completed the pre-measurement and serves as the primary analysis set for this investigation. It represents a solution for managing complications as noncompliance or missing outcomes and therefore reflects the practical clinical scenario [40]. (2) The *per protocol* population (PP): This data set contains all patients who completed the study without or with very minor violations of the regulations according to the study program and is considered a sensitivity analysis. It is considered a protocol violation if less than 9 units of hippotherapy were completed. Analyses for primary and secondary endpoints will be conducted for *m*ITT and PP populations, whereas evaluations based on the PP-population will serve as sensitivity analyses. (3) The third data set includes the safety population and considers AEs; it includes patients who completed at least one treatment, as opposed to the treatment they were randomized to receive. Safety data (AEs) are summarized and documented according to type, severity, intensity and correlation [41].

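### The mixed model named as verification of the primary ANCOVA rests on the same missing-at-random footing, so their agreement says little about bias from drop-out that is not at random

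*Protocol article*

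**What the plan says.** All of the following stands in the Protocol article under Statistical procedures (2.8) unless noted.

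- Primary analysis: "Statistical methods for analyzing the primary outcome of change in balance performance after 12 units of therapy (change from baseline) will be covariance analyses (ANCOVA").
- Primary set: the mITT population, which "comprises all registered patients who completed the pre-measurement and serves as the primary analysis set for this investigation". The text presents it as a way to deal with noncompliance and missing outcomes. It does not say how a missing post BBS enters the ANCOVA.
- Verification: "These analyses shall be verified by sensitivity analyses using linear mixed models (LMMs"). The mixed model is also meant to handle non-independent data and to describe change over therapy and follow-up.
- Covariates: "Therapeutic facility, gender, age, baseline BBS and EDSS score are included in the calculations as co-variables".
- Missing data: "This approach accommodates missing data under the missing at random (MAR) assumption, ensuring that all available measurements are included", and the approach will "therefore provide less biased and more robust estimates".
- Other check: "evaluations based on the PP-population will serve as sensitivity analyses". Fewer than 9 hippotherapy sessions is a per-protocol violation.
- Attrition: 20% is planned for the primary analysis. About 40% is planned for the 70-patient biomechanical/EEG sub-sample.
- Intervention (2.4): attending fewer than 9 of 12 hippotherapy sessions counts as drop-out.
- Assessment (2.7): BBS is measured at baseline, post and follow-up.

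**The concern.** A sensitivity analysis is informative when it changes an assumption that could be wrong. Here the likeliest weak point is drop-out. The nine-session rule can create drop-out only in the hippotherapy arm, so loss may be tied to arm and to response. The mITT set is meant to include patients who stop, so what happens to their balance belongs in the answer.

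An ANCOVA on observed post values is valid if the post value is missing at random given the covariates. The mixed model uses the same covariates and states the same assumption. If patients who left did worse than the models predict for them, both estimates are shifted in the same direction and by nearly the same amount. Their agreement could then be reported as confirmation. The per-protocol set removes patients who stopped, so it does not test the assumption either.

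**Working it through.** **1. The plan's own drop-out figure.** 111 / (1 − 0.20) = 138.75, so 139, rounded to 140. This reproduces. At 20% loss, 140 × 0.80 = 112 patients have a post BBS.

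**2. Why the two estimates coincide under monotone drop-out.** Let x be the covariates (arm, baseline BBS, facility, gender, age, EDSS). A likelihood model for post and follow-up splits as f(post | x) × f(follow-up | post, x). If nobody who misses post returns, the first factor contains only patients with an observed post value. With unstructured covariance and time-specific coefficients, its maximum is the least-squares fit of post on x, which is the ANCOVA. Using change instead of the post value alters nothing, because baseline is a covariate. A baseline-only patient contributes no outcome to either model.

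**3. Simulation of the two models.** Assumptions, not given in the protocol: N = 140, true effect 3.0 points at post, SD 6, correlations .65 to .80, and baseline plus one binary covariate. The mixed model has unstructured covariance; 1,500 runs. In the not-at-random rows, poor responders tend to leave the hippotherapy arm, and control patients leave at random. All rows are at 20% loss.

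| Drop-out | ANCOVA bias | Mixed-model bias | Correlation |
|---|---|---|---|
| Completely at random, monotone | −0.01 | −0.01 | 1.000 |
| Depends on baseline, monotone | −0.02 | −0.02 | 1.000 |
| Not at random, monotone | +1.11 | +1.11 | 1.000 |
| Not at random, half return at follow-up | +1.11 | +0.87 | .969 |

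In the monotone rows the two estimates were the same in every run (largest difference 0.00). In the last row about 15 extra patients enter the mixed model. The estimate moves by 1.11 − 0.87 = 0.24 points, or 0.24 / 1.11 = 22% of the bias. The run-to-run SD of the ANCOVA estimate is 0.79, so a gap of 0.24 would not stand out.

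A smaller simulation (150 runs, residual SD 4.26, random-intercept model, a little sporadic missingness) gave 3.00 for the ANCOVA and 2.99 for the mixed model where the true mITT effect was 2.46. The correlation was .99. Near-agreement therefore does not depend on the unstructured covariance.

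**4. Possible size at the planned 20%.** Let d = 0.20 be the share of the hippotherapy arm that stops (assuming the planned rate holds in that arm), r the share of the effect they keep, m the share of them measured at post, and E the effect in those who stay. Assume stoppers otherwise resemble stayers with the same covariates.

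- True mITT effect = E × [1 − d(1 − r)]
- Observed-case estimate = E × [(1 − d) + d·m·r] / [(1 − d) + d·m]

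| m | r | True effect | Estimate | Overstatement |
|---|---|---|---|---|
| 0 | 0 | 0.80 E | E | 1 / 0.80 = 1.25, so 25% |
| 0 | 0.5 | 0.90 E | E | 1 / 0.90 = 1.11, so 11% |
| 0 | 1 | E | E | none |
| 0.5 | 0 | 0.80 E | 0.80 / 0.90 = 0.89 E | 0.89 / 0.80 = 1.11, so 11% |
| 1 | 0 | 0.80 E | 0.80 E | none |

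In points, for the first row: with E = 3.07 (the difference used to size the sub-sample) the true effect is 3.07 × 0.80 = 2.46, so estimate and truth lie on opposite sides of the 3-point MCID. With E = 4.61 (the per-protocol difference from the preliminary study) it is 4.61 × 0.80 = 3.69, and both lie above 3.

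**The case against.** The strongest reply has four parts.

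- **The detail may sit elsewhere.** Analyses that depart from MAR are often left to an analysis plan, which is not shown, and the article states MAR openly. This stands to the extent that absence alone would be no finding. The point rests instead on what the article does state: that the mixed model verifies the primary result and is less biased.
- **The ANCOVA's handling of missing values is not given.** MAR is written for the mixed model only. If the mITT ANCOVA imputes post values, the two analyses could differ. This stands, and the conclusion is conditional on observed-case analysis.
- **Stoppers may be measured.** The article calls fewer than nine sessions a drop-out in one place and a per-protocol violation in another. It does not say whether these patients attend the post assessment. If they do, their lost benefit enters the ANCOVA and the bias from them disappears. This stands, which is why the range starts at none.
- **The mixed model has other uses.** It deals with clustering and the course to follow-up, and with returning patients it is somewhat less biased (+0.87 against +1.11). This also stands.

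Two stronger readings are tempting and should be resisted. A reader might infer that the models must agree automatically; that is exact only for monotone drop-out, and returning patients separate them a little. A reader might also take drop-out as 20% to 40%, with an overstatement of up to 67% (1 / 0.60 = 1.67). But 40% is the planning rate for the biomechanical/EEG sub-sample, taken from the preliminary study's per-protocol loss, and the primary analysis plans for 20%.

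**Conclusion.** The concern holds in limited form. As described, the mixed model is a reasonable check on model structure but a poor check on missing-data bias. Its agreement with the ANCOVA should not be read as protection against drop-out that is not at random, and the per-protocol analysis does not supply that protection.

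The conclusion assumes an observed-case ANCOVA and baseline BBS as a covariate in both models. The 25% upper end restates the assumption that stoppers are unmeasured and keep no benefit; it is not a forecast. Whether the 3-point MCID is crossed depends on the effect assumed. The simulated biases depend on the assumed SD, correlations and drop-out mechanism; the identity under monotone drop-out does not. The documents do not show that the primary estimate will be biased, only that the stated verification would be unlikely to reveal it. Nothing here changes the primary analysis itself.

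**What to change.** - Keep the mixed model, described as the analysis of clustering and of the course to follow-up.
- Remove the claim that it verifies the primary result against missing-data bias. Limit the less-biased statement to what holds under MAR when patients return at follow-up.
- State how the mITT ANCOVA treats a missing post BBS, since the comparison depends on it.
- Pre-specify one mITT sensitivity analysis that departs from MAR: multiple imputation of missing 12-week BBS in the hippotherapy arm from the control-arm distribution, with a delta shift. Report the shift at which significance is lost and the shift at which the estimate falls below 3 points.

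The cost is a few lines of text and a short program, with no new data. It should be fixed before results are known. The downside is a little extra analysis and a sensitivity estimate that may be less favourable than the ANCOVA.
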